#### Hypotheses

We propose the following hypotheses:

H1: Participants will rate N-ACT as an acceptable intervention to reduce emotion dysregulation.H2: Participants will demonstrate adherence to the N-ACT program at levels comparable to those observed in established cognitive remediation protocols [33,52,62-64].H3 (primary): Compared to baseline, participants assigned to complete N-ACT (without a waitlist) will report greater decreases in rumination and ERI at the postintervention assessment than those assigned to the control condition at the postwaitlist assessment.H4 (secondary): Compared to baseline, participants assigned to complete N-ACT (without a waitlist) will demonstrate greater improvements in targeted affective control processes (ie, enhanced emotional working memory and emotional response inhibition) at the postintervention assessment than those assigned to the control condition at the postwaitlist assessment.H5 (secondary): Compared to baseline, participants assigned to complete N-ACT (without a waitlist) will demonstrate near (ie, enhanced hot affective flexibility) and far (ie, enhanced cold working memory and cold response inhibition) transfer of trained neurocognitive abilities at the postintervention assessment than those assigned to the control condition at the postwaitlist assessment.H6 (secondary): Compared to baseline, participants assigned to complete N-ACT (without a waitlist) will report greater decreases in self-rated psychopathology symptom severity (ie, reduced internalizing and externalizing symptoms) at the postintervention assessment than those assigned to the control condition at the postwaitlist assessment.

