#### Statistical Analysis Plan

Our final target sample size (*n*=80) was derived from power analysis (1-β>0.85), based on hypothesized medium between-groups effect sizes (Cohen *d=*0.35) for the main outcomes of interest (α=.05). Before conducting the analyses, data will be checked for errors, statistical assumptions, and potential confounding variables to examine as covariates. Missing data imputation will also be performed as appropriate; we will present the results with and without imputed values for comparison. Our primary analyses will follow the International Conference on Harmonization E9 statistical principles for clinical trials. In accordance with these principles, we will use intention-to-treat analyses to estimate the main effects of N-ACT, using the final assessment scores of all randomized participants. To augment these findings, we will conduct sensitivity analyses restricted to data from participants who complete preintervention and postintervention assessments and at least 6 of the 8 weekly N-ACT sessions.

Descriptive statistics will be calculated to address the preliminary hypotheses regarding N-ACT’s acceptability and adherence. Mean scores on the Interest or Enjoyment and Value or Usefulness subscales of the adapted Intrinsic Motivation Inventory [82] will serve as our main indices of the N-ACT program’s acceptability (H1); specifically, we predict that participants who complete the intervention will provide average ratings of at least 5 (out of 7) across both scales. We further hypothesize that N-ACT participant adherence and retention will be comparable to those observed in other cognitive remediation interventions (H2); specifically, we anticipate median person-level adherence levels between 70% and 75%, which we expect to decrease at the group level by approximately 5% each week [63,64], with most participants (ie, >66%) completing all 8 N-ACT training sessions [33,52]. Consistent with other cognitive remediation protocol procedures [63], we will calculate percentage adherence for each participant as a function of the number of *completed* N-ACT training task trials divided by the *total* number of trials, that is, individual differences in the “dosage” of training.

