We will consider potential confounds before testing key hypothesized effects. Of particular import, we will examine whether participants differ significantly in treatment gains based on assignment to a specific training coach and control for this unintended influence as necessary. Specifically, we will use multivariate analysis of covariance (MANCOVA) to explore the effect of coach assignment (independent variable) on postintervention emotion dysregulation (ie, scores on the TFII-FTA and RRS-B; dependent variables), controlling for scores at initial screening.

The core aim of this pilot trial is to determine whether N-ACT significantly reduces ERI and rumination, as measured by the TFII-FTA and RRS-B, respectively (H3). To achieve this aim and the related objective to explore potential mechanisms, we will conduct parallel 2 (group: immediate N-ACT vs waitlist control condition; between-subjects factor)×2 (time: T1 vs T2; within-subjects factor) mixed MANCOVAs to evaluate whether N-ACT completion is associated with greater pre-postintervention improvement in these 2 primary outcomes compared to the waitlist control condition. Among all participants, T1 will represent data collected at the baseline assessment; for participants assigned to the immediate N-ACT group, T2 refers to the postintervention assessment, whereas for those assigned to the control condition, T2 refers to the postwaitlist assessment. Thus, these models will not include postintervention data for participants initially allocated to the waitlist, permitting direct comparisons of the slope of change over time associated with completing N-ACT or the waitlist period. The key index of treatment effect in all MANCOVA models will be the group×time interaction. We will also perform a parallel set of multivariate cluster-robust general linear models with time (T1: baseline time point vs T2: postintervention time point) as the sole regressor on key outcomes of interest, which will include all participants who complete N-ACT (regardless of initial group or condition assignment) to maximize statistical power.

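### The primary group×time test for H3 is a raw change-score comparison that gives up precision, and, if run as one joint model, cannot by itself show that rumination and impulsivity both fall

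*Protocol article*

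**What the plan says.** H3, labelled primary in the Hypotheses section, predicts that participants given N-ACT without delay "will report greater decreases in rumination and ERI at the postintervention assessment than those assigned to the control condition at the postwaitlist assessment". The Statistical Analysis Plan section repeats this as the core aim: to "determine whether N-ACT significantly reduces ERI and rumination, as measured by the TFII-FTA and RRS-B, respectively (H3").

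The analysis is a mixed model with group as the between-subjects factor and time as the within-subjects factor. For everyone, "T1 will represent data collected at the baseline assessment"; T2 is the postintervention assessment in the N-ACT arm and the postwaitlist assessment in the control arm. The section describes this as "permitting direct comparisons of the slope of change over time associated with completing N-ACT or the waitlist period", and then fixes the effect measure: "The key index of treatment effect in all MANCOVA models will be the group×time interaction".

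No covariate is named for this model. The section says only that "data will be checked for errors, statistical assumptions, and potential confounding variables to examine as covariates". The one explicit adjustment for earlier scores, using screening values, belongs to the separate check for coach effects.

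**The concern.** Two things are at stake.

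The first is precision. Treating T1 as a level of the time factor fixes the baseline slope at 1 instead of estimating it. In a randomised trial, a comparison of T2 adjusted for T1 targets the same group difference with smaller variance, using data the trial already plans to collect. With about 40 completers per arm there is little precision to spare.

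The second is what a significant result would mean. H3 and the core aim are conjunctive and directional: rumination and impulsivity are both to fall. A multivariate interaction on the two outcomes rejects when any combination of them differs between arms, in any direction. If that single test is the key index, a significant result is compatible with only one outcome changing, or with one improving while the other worsens.

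**Working it through.** **Inputs.** From the article: N=80, 1:1 allocation, 40 completers per arm, d=0.35, α=.05, stated power above 0.85, 20% attrition. Assumed because the article does not give them: two-sided testing; the T1–T2 correlation rho; the correlation r between the two outcomes (taken as the same within each time point and for the changes); equal SDs at T1 and T2.

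**The plan's own figure.** The attrition step reproduces: 80/(1−0.20)=100. The power does not. For a between-groups d=0.35, the noncentrality is 0.35×√(40/2)=1.565, giving power of 0.34 two-sided (0.46 one-sided) on 78 df; 85% would need 147 per arm. That is a separate matter and is used here only to show how little precision is available.

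**Interaction and change score.** The interaction contrast is (mean T2 − mean T1) in the N-ACT arm minus the same quantity in the waitlist arm, which is the difference in mean change. On one simulated 2×2 data set, the interaction F and the squared change-score t were both 6.4845.

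**Variance.** With common variance σ², a change score has variance 2(1−rho)σ², and T2 adjusted for T1 has (1−rho²)σ². The ratio is (1−rho²)/[2(1−rho)] = (1+rho)/2. Noncentrality is 0.35×√20/√[2(1−rho)] for change and 0.35×√20/√(1−rho²) for adjustment.

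| rho | variance ratio | power, change | power, adjusted | n per arm for 85%, change / adjusted |
|---|---|---|---|---|
| 0.3 | 0.65 | 0.26 | 0.37 | 206 / 134 |
| 0.5 | 0.75 | 0.34 | 0.43 | 147 / 110 |
| 0.6 | 0.80 | 0.41 | 0.49 | 118 / 94 |
| 0.7 | 0.85 | 0.51 | 0.58 | 88 / 75 |
| 0.8 | 0.90 | 0.69 | 0.73 | 59 / 53 |

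Below rho 0.5 the change score is less precise even than comparing T2 scores alone, because 2(1−rho) then exceeds 1.

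**Joint test.** For two outcomes, the multivariate interaction is Hotelling's test on the changes, referred to F(2, 77). For effects a and b in SD units, the noncentrality is [20/(2(1−rho))]×(a²+b²−2rab)/(1−r²). At rho 0.5 the first factor is 20:

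| true effects (SD) | noncentrality, r=0.3 / 0.5 | rejects, rho 0.5 | rejects, rho 0.7 |
|---|---|---|---|
| one improves 0.35, other 0 | 2.69 / 3.27 | 28% / 34% | 44% / 52% |
| one improves 0.35, other worsens 0.35 | 7.00 / 9.80 | 64% / 79% | 86% / 95% |
| both improve 0.35 | 3.77 / 3.27 | 38% / 34% | 59% / 52% |

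At r=0.5 the test cannot tell one outcome moving from both moving: the noncentrality is 3.27 in each case. When both truly improve by 0.35 SD, each outcome is individually significant in the same trial in only 15-19% of simulated trials at rho 0.5 and 31-35% at rho 0.7.

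**If there is instead one model per outcome.** Two tests at .05, with success on either counting, give a familywise error of 1−0.95²=9.75% if independent, and about 9 to 9.5% at r of 0.5 to 0.3.

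**The case against.** The planned interaction is unbiased under randomisation and holds its nominal error rate, and H3 is itself worded as change from baseline, so test and hypothesis agree. This stands: the first half of the point concerns precision, not validity. A reader might infer that the change-score analysis is wrong; the document does not support that.

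The model is called a MANCOVA, and covariates are to be examined. If the T1 score were entered, the interaction would become the adjusted test. But the article does not name it, and the covariates it mentions are potential confounders.

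The article speaks of *parallel* MANCOVAs, which may mean one model per outcome. Per-outcome follow-up tests and a multiplicity rule may also sit in the preregistration or an analysis plan not shown. This stands too, so the joint-test half is conditional. A reader might infer that the trial will report a significant joint test as both outcomes falling; nowhere does the article say so.

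The opposite-direction case is an illustration. Nothing in the article predicts it, and opposite effects on positively correlated outcomes favour this test. It shows what a rejection cannot exclude, not what is likely. A more striking figure comes from 0.70 SD on one outcome and none on the other (82-99% rejection for rho 0.5 to 0.7), but that is twice the plan's effect size and should not carry the argument.

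Finally, this is a pilot. It nevertheless labels H3 primary and makes a significance claim its core aim.

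**Conclusion.** The point holds in two parts of unequal certainty.

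First, as written, the key index is a change-score comparison, and adjusting for T1 would reduce variance by 25% at rho 0.5, 20% at 0.6 and 15% at 0.7 at no cost in data. The gain is moderate: at d=0.35 it adds 7 to 9 percentage points of power across that range and does not bring the trial near 85%. These figures rest on an assumed rho and two-sided testing.

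Second, if the MANCOVA is a single joint model of RRS-B and FTA, its interaction test alone cannot support the conjunctive, directional H3. If there is one model per outcome, that objection falls away, and what remains is that the article gives no rule for what counts as success on two primary outcomes. The protocol should be revised on both parts, but neither makes the planned test invalid.

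**What to change.** Make the primary H3 analysis one baseline-adjusted comparison per outcome: T2 RRS-B on group and T1 RRS-B, and likewise for FTA, or the equivalent baseline-constrained mixed model. Report each estimate with a 95% CI. State the source of the T1 score explicitly, because Table 1 appears to tick both measures at screening rather than at baseline, while the analysis text takes T1 from baseline.

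State the decision rule: claim that both fall only if each comparison is significant at two-sided .05 in favour of N-ACT; otherwise claim one alone only if it is significant at .025 (Hochberg). Keep the MANCOVA as supportive.

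The cost is wording only, with no added participants or measures. A claim of both is harder to reach than a joint rejection. With 0.70 SD on each outcome at rho 0.5, power for both is about 0.77 to 0.79 before the gain from adjustment, against 0.90 to 0.94 for the joint test. At 0.35 SD on each it is only 0.15 to 0.19 at rho 0.5.

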After the baseline assessment (laboratory session, questionnaires, and EMA), we will randomly assign participants to receive active treatment (ie, N-ACT without delay) or the waitlist control condition, unblinded, using an asymptotic maximal procedure to achieve a maximally tolerated imbalance of 2, while maintaining a 1:1 allocation ratio between the 2 trial arms [63]. Participants in the active N-ACT group will begin the intervention, which consists of 8 weekly coached training sessions, within 1 week after baseline EMA. We will recontact waitlist control participants after a period equivalent to the intervention duration (ie, 2 months) to complete a second (postwaitlist) assessment session and EMA before starting the N-ACT program for the following 8 weeks. After the intervention, participants will be asked to complete a second week of EMA, and then a postintervention assessment session with comparable measures to baseline. We will recontact waitlist control participants approximately 10 weeks after their (prewaitlist) baseline assessment session to complete a second (postwaitlist) assessment and 1 week of EMA, parallel with the pre-intervention assessment procedures of the N-ACT group,. The waitlist group will then be offered 8 weeks of N-ACT, followed by a second week of postintervention EMA, and then a final assessment session. In sum, we will follow participants assigned to receive the intervention without delay for 12 weeks (3 mo) and those assigned to the waitlist control group for 22 weeks (5.5 mo). This delayed intervention randomized waitlist-controlled trial design enables us to offer all interested participants the opportunity to participate in the program and maximizes our ability to rapidly accrue a sufficiently sized sample for analyses. Figure 1 demonstrates the flow of potential participants through the study procedures.

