### Study Procedures

#### Recruitment and Screening

We will invite up to 500 adults to complete preliminary screening procedures and an estimated 100 participants to complete the initial baseline assessment session. After accounting for 20% expected attrition, we expect 40 participants in each condition to complete all study procedures.

Study advertisements will be posted locally in public spaces and distributed by web (eg, via email listserves, Craigslist, and social media sites). We will also administer a prescreening survey to students enrolled in psychology classes at the University of California Berkeley, and we will invite students who meet the preliminary inclusion criteria based on those responses to take part in the study. Potential participants (recruited either from the community or from the student participant pool) will be directed to our website, where they can view additional details about the trial. We intend to recruit only secondarily from the student participant pool to supplement community-based recruitment, which will constitute most of the targeted sample. All questionnaires, including screening items, will be administered through REDCap (Research Electronic Data Capture; Vanderbilt University) software [65], which will also be used for the secure storage of collected data.

After providing informed consent, interested individuals will complete the brief web-based screening via REDCap to assess preliminary eligibility. The inclusion and exclusion criteria are presented in Textbox 1.

Inclusion and exclusion criteria.

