In addition to testing the hypothesized effects on emotion dysregulation, mixed MANCOVA and multivariate cluster-robust general linear models will be used to evaluate performance changes over time on (1) 2 hot executive functioning tasks (ESST and MAFT), which will be used to assess the hypothesized effects on the targeted aspects of affective control (H4); and (2) one hot (MAFT) and 2 cold (Digit Span Backward and SST) executive functioning tasks, which will be used to ascertain transfer to the nontargeted cognitive processes (H5). We will specifically derive key dependent variables from the ESST (valence-specific indices of stop-signal reaction time) and the MAFT (valence-specific indices of accuracy) to assess intervention-related changes in emotional response inhibition and emotional working memory, respectively. We will similarly calculate summary metrics of hot affective flexibility from the MAFT (valence-specific indices of accuracy and reaction time on less frequent “switch” trials prompting emotional reactions instead of working memory recall [73]) as well as cold working memory, updating from the Digit Span Backward (mean span) and cold response inhibition from the traditional SST (stop-signal reaction time) to evaluate near and far transfer of hypothesized N-ACT training effects, respectively.

Finally, we will perform a complementary set of secondary analyses (ie, mixed MANCOVA and multivariate cluster-robust generalized linear models) to explore the hypothesized downstream effects of N-ACT on changes in psychiatric symptom severity (H6). We will use dimension-reduction techniques (eg, confirmatory factor analysis) to extract the summary indices of internalizing and externalizing symptoms from the Inventory of Depression and Anxiety Symptoms, Expanded Version and ESI-R, respectively. Statistical models will use these latent factors as dependent variables, potentially providing preliminary evidence for the efficacy of affective control training as a transdiagnostic intervention to address psychopathology (via diminished emotion dysregulation; refer to Multimedia Appendix 1 for more information). Support for this hypothesis will motivate future work to more directly and precisely examine the effectiveness of the N-ACT program in sufficiently powered samples of patients with psychiatric conditions.

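### The pooled before-after model in N-ACT completers has no comparator, so it cannot test H3–H6 and should be reported as descriptive only

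*Protocol article*

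**What the plan says.** The Statistical Analysis Plan section first describes a 2×2 mixed MANCOVA (immediate N-ACT or waitlist, by T1 or T2). It keeps waitlisted participants' post-training data out of that model and makes the group×time interaction the key index of treatment effect in the MANCOVAs.

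It then adds a parallel set of cluster-robust models with time (baseline against postintervention) "as the sole regressor on key outcomes of interest, which will include all participants who complete N-ACT (regardless of initial group or condition assignment"). The stated reason is power. For the cognitive tasks (H4, H5), "mixed MANCOVA and multivariate cluster-robust general linear models will be used to evaluate performance changes over time", and the paragraph on H6 names the same pair of models. Nothing says that the time-only models are descriptive, or which result prevails if the two disagree.

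Three other places bear on this:

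- **Hypotheses.** H3 to H6 each set the immediate arm's change at postintervention against the control arm's change at postwaitlist.
- **Methods, Overview.** The waitlist arm's baseline comes before the waiting period. A postwaitlist assessment follows about 10 weeks later, before training starts. The immediate arm is followed for 12 weeks and "those assigned to the waitlist control group for 22 weeks (5.5 mo").
- **Statistical Analysis Plan, first paragraph.** The main effects are to be estimated by intention to treat in everyone randomised.

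**The concern.** A model whose only regressor is time estimates the raw before-after change. Cluster-robust standard errors allow for repeated measures on the same person; they do not separate the intervention from whatever else changed. Natural course, practice on a repeated task battery and selection of people who finish the programme all enter the coefficient. Practice weighs more in the waitlist arm, which meets the battery for the third time at postintervention.

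The model stands next to the randomised test for H3–H6 with power as its justification. A clear time effect beside an inconclusive interaction could therefore be read as support for efficacy. The Discussion expects this pilot to inform a fully powered trial, so such a reading would carry forward.

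**Working it through.** **1. Can the model address the hypotheses?** H3–H6 concern (change in immediate arm) − (change in waitlist arm). Write the change with training as *effect + other change*, and the change while waiting as *other change*. The group×time interaction estimates the difference, which is *effect* when the other change is equal in both arms. The time-only coefficient estimates *effect + other change*, and nothing in that model separates the two.

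**2. Intervals, taking T1 as baseline in both arms.**
- Untreated excess in the waitlist arm: 22 − 12 = 10 weeks, and 10/22 = 45% of its interval.
- Mean interval with equal numbers from each arm: (12 + 22)/2 = 17 weeks. A steady natural improvement would enter at 17/12 ≈ 1.4 times its 12-week size.
- Starting the waitlist arm at the postwaitlist assessment gives 22 − 10 = 12 weeks, the same as the immediate arm.

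**3. The plan's own power figure.** The article gives none for the pooled model. The sample size "was derived from power analysis (1-β>0.85), based on hypothesized medium between-groups effect sizes" of d = 0.35, with α = .05 and 40 completers per arm. A two-sided two-sample calculation has noncentrality 0.35 × √(40/2) = 1.565 and power 0.347, so it does not reproduce the stated value. A one-group paired test of 80 people with d = 0.35 and SD of change 1 has noncentrality 0.35 × √80 = 3.13 and power 0.871. A group×time calculation with f = d/2 = 0.175 and correlation 0.5 also gives 0.871. The present point does not rest on this. It does show how much larger the power looks once the comparator is dropped.

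**4. How often would the pooled test be significant with no N-ACT effect?**
- From the article: 80 completers (40 per arm). The figure of 66 takes its expectation that more than 66% finish all eight sessions, applied to the 100 people at baseline: 0.66 × 100 = 66.
- Assumed, because the article gives neither: general improvement δ of 0.10 or 0.20 SD; T1–T2 correlation ρ of 0.5 or 0.7.
- Test: two-sided 5% paired t-test on one outcome. SD of change = √(2(1 − ρ)), which is 1.000 at ρ = 0.5 and 0.775 at ρ = 0.7. Noncentrality = δ√n / SD of change.

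| n | ρ | noncentrality (δ = 0.10; 0.20) | significant (δ = 0.10; 0.20) |
|---|---|---|---|
| 66 | 0.5 | 0.81; 1.62 | 13%; 36% |
| 80 | 0.5 | 0.89; 1.79 | 14%; 42% |
| 66 | 0.7 | 1.05; 2.10 | 18%; 54% |
| 80 | 0.7 | 1.15; 2.31 | 21%; 63% |

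With δ = 0 the rate is 5%. An equal shift in both arms cancels from group×time; in a two-outcome simulation (800 runs per setting) that test scattered around 5%, from 3.4% to 7.4%.

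**5. Regression to the mean.** Entry requires a high score on RRS-B or FTA, the two primary outcomes. In the same simulation (80 people, no drift, assumed reliability 0.7–0.9, assumed cut-off 0–1 SD above the population mean), the pooled test was significant in 9–87% of runs when the screening score served as T1. It was significant in about 5% when T1 was a separate later measurement. Table 1 as extracted ticks RRS-B and FTA at screening but not at baseline, while the section on the Three-Factor Impulsivity Index implies that FTA is measured at baseline. The table may be damaged, so this source of bias is conditional.

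**The case against.** The strongest reply is that the model is an addition. The randomised MANCOVA comes first, the commitment to intention to treat covers the main effects, and group×time is the key index there. This is a pilot, and the H6 models are called secondary. All of that stands. A reader might infer that the efficacy test itself is compromised, or that every hypothesis gets an uncontrolled second test. The text does not support either: the MANCOVA is intact, and H1 and H2 are descriptive.

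A reader might also take it as settled that waiting time is counted as treatment. The sentence fixing T1 as baseline for everyone describes the MANCOVAs, and the Methods Overview also allows T1 to be the preintervention time point. The literal reading is the more natural one, since the pooled model itself names baseline, but the ambiguity is real.

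Thirdly, it is tempting to say that the waitlist arm's last assessment adds nothing to the treatment contrast. That holds only if time is a free categorical effect. With a structured time trend, or a within-person comparison of waiting change with training change, that assessment is informative.

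Finally, the percentages in step 4 are not type I error rates of the pooled test. If scores really improved, rejecting no change is correct; the error lies in crediting N-ACT. They also depend on assumed drift and correlation, and they use one outcome where the plan is multivariate.

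**Conclusion.** The concern holds for the pooled model and should be corrected; the randomised analysis needs no change on this account. The pooled model cannot test H3–H6 for want of a comparator, and this needs no numerical assumption. Its restriction to completers is stated outright, with completion left undefined for this model. Counting about 10 untreated weeks in the waitlist arm follows from the literal wording, which needs clarifying.

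The size is illustrative. With no N-ACT effect and an assumed general improvement of 0.10–0.20 SD, significance occurs in 13–42% of trials at correlation 0.5 and 18–63% at 0.7, over 66 to 80 completers. Regression to the mean would add to this for RRS-B and FTA only if screening scores serve as T1.

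**What to change.** - State that efficacy conclusions for H3–H6 rest only on the randomised T1–T2 group×time comparison.
- Report the pooled before-after change as descriptive and uncontrolled, with an estimate and confidence interval and no claim of efficacy.
- In it, use the postwaitlist assessment as the pre-training value for waitlisted participants.
- Include everyone who starts N-ACT. The Questionnaires section already plans to ask people who withdraw early to complete the main self-report outcomes.
- Show the result beside the waitlist arm's untreated T1–T2 change.

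This changes analysis wording only and uses assessments already planned. What is lost is an apparent power gain that comes from attributing all change over time to N-ACT.
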